## 1 - INTRODUCTION

Fibromyalgia (FM) is a syndrome of widespread musculoskeletal pain which is characterized by the presence of at least 11 of 18 tender points, sleep disturbance and fatigue of chronic evolution (Wolfe et al., 1990; Brosseau et al., 2008). It is reported in 2-5% of the Brazilian population (Senna et al., 2005; Pereira et al., 2009) and represents 18.2% among the individuals with musculoskeletal non traumatic chronic pain in the state of Espírito Santo (Pereira et al., 2009). It affects 2 to 4% of the American population and the majority is women. People at any age may develop FM but they are more likely to have it between ages 35 to 50. (Heymann et al., 2006; Martinez et al., 2007). The prevalence of FM is probably greater than the one found in epidemiological studies. This is because these studies used the ACR 90 criteria which include the presence of tender points. (Wolfe et al., 1990). Nevertheless, there are many patients with fibromyalgia with diffuse pain without tender points and there are also patients with myofascial pain, making part of the fibromyalgia spectrum. In a Brazilian study the prevalence of FM defined by the diffuse pain with or without tender points was 5.5% (Pereira et al., 2009). In addition, this syndrome includes many symptoms which might fragment the evaluation and delay the diagnosis whenever some of them specifically prevails such as fatigue, pain, muscle weakness, memory problems, paresthesias, headaches, depression, anxiety, irritable bowel syndrome, dysmenorrhoea, subjective swelling, urethral syndrome, abdominal pain, sicca syndrome and they are all attributed to the autonomic nervous system dysfunction (Brosseau et al., 2008, Part 1; Hammond and Freeman, 2006; Gowans et al., 2002).

According to the majority of researchers (Penrod et al., 2004; Busch et al., 2007; 2009; Geel et al., 2002; Valim, 2003; Valim, 2006), the incapacity rate among people with FM is 46% and there are important social costs such as the direct ones (medicines, doctor's appointments, lab and image exams) and the indirect ones (absences from work, job loss, the need of help to do the activities at home).

The eferent peripheral division of the Autonomic Nervous System (ANS) is represented by two components: sympathetic and parasympathetic which have antagonistic actions in the changes of body functions. This event enables the homeostasis maintenance particularly over the Heart Rate (HR) control.

In FM an abnormal sympatho-vagal balance is observed and Heart Rate Variability (HRV) is reduced. This fact increases the risk of cardiovascular morbidity and mortality (Coelho PF, 2008; Petzke and Clauw, 2000) .

Several clinical manifestations presented in FM such as fatigue, morning stiffness, sleep dysfunctions, anxiety, depression, sicca syndrome; irritable bowel syndrome and Raynaud's phenomenon could be explained by the dysautonomia. Due to these clinical characteristics which are compatible with ANS modulations, some studies associate the involvement of this system in the physio-pathogenesis of FM (Tak et al., 2009; Dogru et al., 2009; Coelho PF, 2008).

Several ways of measuring the autonomic activity have been studied and validated as:

- 1 – Electromyography of small fibers
- 2 – Cardiac Doppler under stress conditions and cold temperatures exposure
- 3 – Catecholamine dosages
- 4 – Orthostatic tests such as the Tilt Table Test
- 5 – Heart Rate Variability (HRV) through the evaluation system of the American European Task Force (Task Force, 1996)
- 6 – COMPASS questionnaire (The Composite Autonomic Symptom Scale)

The proposal of autonomic dysfunction in the main role in the pathogenesis of FM is based on several research lines. The most consistent works have support in analysis of Heart Rate Variability (Solano et al., 2009 ; Tak et al., 2009 ; Figueroa et al., 2008; Furlan et al., 2005; Martinez,2001).

This kind of analysis showed HRV alterations compatible with sympathetic hyperactivity in many studies. The excessive sympathetic activity is followed by a minor response to different kinds of orthostatic stressors (Ozgocmen et al., 2006; Furlan et al., 2005 ; Petzke and Clauw, 2000).

Solano et al., in 2009, demonstrated that there is a correlation between the questionnaires that measure the impact of quality of life in FM (FIQ) and the questionnaire that assesses the autonomic dysfunction (COMPASS). The severity of FM is related to the multiple painless symptoms related to different expressions of dysfunction of ANS. Such correlation suggests that the autonomic dysfunction is an essential characteristic of FM.

Patients with FM have a high score in the psychosomatic evaluation of COMPASS. This likely reflects the presence of anxiety and depression, two psychosomatic components which might lead these patients to overestimate their symptoms.

The symptoms of chronic diffuse pain, allodynia and paresthesias in FM are attributed to persistent sympathetic activity. The chronic fatigue may be explained by the “ceiling effect” of the sympathetic hyperactivity in addition to “desensibilization” of adrenergic receptor.

Nowadays the most stressful type of life might contribute for a continuing sympathetic hyperactivity and individuals with a system of degradation of catecholamine genetically slow may have a greater risk of developing FM (Vargas-Alarcon et al., 2007).

The recent Brazilian Consensus for the treatment of fibromyalgia (Heymann et al., 2010), based on evidence, establishes that patients with FM must be treated with tricyclic antidepressants (amitriptyline or cyclobenzaprine) or selective antidepressants, preferably “dual”, either associated or not to anticonvulsants. Analgesics may be taken if necessary. Physical exercises and cognitive-behavioral therapy compose complementary treatment and might benefit some patients. The strategy to the ideal treatment is a multidisciplinary approach with the combination of pharmacological and non-pharmacological treatment modalities (Koulil et al., 2006; Heymann et al., 2010).

Over the last 20 years some clinical trials have been published about exercises on the treatment of FM. In 2008 an extensive review was concluded by a great team of researchers from Ottawa Hospital Research Institute which resulted in the Ottawa Panel Evidence-Based Clinical Practice Guidelines for Aerobic Fitness Exercises in the Management of Fibromyalgia: Part 1 (Brosseau et al., 2008) and the Ottawa Panel Evidence-Based Clinical Practice Guidelines for Strengthening Exercises in the Management of Fibromyalgia; Part 2 (Brosseau et al., 2008). Both studies (Part 1 and 2) had the objective of providing information from the treatment outcomes with strengthening and aerobic exercises in FM with evidence level for the prescription guidance of rheumatologists, physiatrists, physiotherapists, occupational therapists, kinesiologists and other professionals who might contribute for the syndrome treatment. The review evaluated aerobic fitness (Dadabhoy and Clauw, 2006) and combined or associated programs to medication treatment or other non-pharmacological interventions. (Isomeri et al., 1993; Cedraschi et al., 2004; Sencan et al., 2004). Stretching exercises were used as control intervention in few studies (Jones et al., 2002; Nativig et al., 1998, Pollock et al., 1998). Few evaluated strength training (Jones et al., 2002; Kingsley et al., 2005; 2009; Figueroa et al., 2008), all of them with a small sample size.

Strengthening exercise is defined as isometric, isokinetic or with concentric/eccentric resistance with the purpose of increasing the maximal strength produced by a specific muscle or muscle group. It may be performed by the help of machines, free weights, balls (Rooks et al., 2002; Tritschler, 2003; ACSM, 2010).

The strength evaluation is specific for muscle groups that are being tested. It is difficult to generalize on the global strength from the result for a muscle group. Some authors believe that the test of 1 RM of supine lift is the best isolated test to predict the global dynamic strength. (Tritschler, 2003; ACSM, 2010). If two tests are used to assess the dynamic strength, the supine lift must be used for the strength of the superior part of the body and the “leg press” for the inferior part (Tritschler, 2003; ACSM, 2010).

Muscle strength is basic for daily activities. The muscle strength training can improve functional capacity, bone mass, fatigue and pain (Hakkinen, 2001;2002; Valkeinen et al., 2004; 2005;2008; Brosseau et al., Part 2, 2008).

Aerobic fitness is the most studied type of exercise and with the highest evidence level for the treatment of fibromyalgia. (Busch et al., 2007; Brosseau et al., Part 1, 2008). There are evidences that supervised aerobic fitness can benefit patients with fibromyalgia, improving pain and quality of life. Stretching exercises also showed benefits in the control groups in pre-post analysis. In relation to strengthening exercises, Ottawa Panel demonstrated that there are emerging evidences that they are safe and can be beneficial. However, there is a necessity of more clinical trials of strengthening exercises with a sample size more suitable in order to assess the clinical effects of them in the treatment of FM. Yet, the physiological and physio-pathogenesis mechanisms that explain the benefit of exercise in the control of chronic pain remain controversial in the literature.

Exercises have a potential to decrease the inactivity and lack of fitness which are factors theoretically related to the pain threshold reduction. They can also improve

associated psychological factors. Strength or strenghtening exercise training can help patients to perform aerobic exercise more easily. (Jones et al., 2002; 2009). Moreover, it is observed that fatigue, more than pain, worsens the quality of life in fibromyalgia. These reasons could explain the reason why strength gain might promote a better quality of life (Valkeinen et al., 2008; Busch et al., 2007).

There are preliminary non control studies with a very small sample size (up to 10 subjects) showing that strengthening exercises improve strength, cardiac parasympathetic tone, HR variability, muscle resistance and increase the pain threshold as well (Figueroa et al., 2008; Kingsley et al., 2009;2010).

Although physical exercises are the most suggested and studied complementary therapy, further studies are still necessary to indicate a better prescription plan that assess the clinical effects of strength training and the mechanisms involved in the therapeutic outcomes.

Our hypothesis is that strength training exercises using prescription parameters well defined and according to ACSM can improve pain, associated symptoms and quality of life and that heart rate variability modulation, namely a better autonomic control, is one of the involved mechanisms in the pain control promoted by this type of exercise in fibromyalgia.

## 2 - OBJECTIVES

### 2.1 - Main

- To study Heart Rate Variability (HRV) in patients with FM who underwent strengthening exercise program comparing to control groups that underwent flexibility and stretching exercises.

### 2.2- Secondary

- to assess the strengthening training outcomes in the improvement of symptoms, quality of life and HRV in patients with FM, compared to control group that underwent stretching and flexibility exercises.
- to assess whether there is an association between strength gain and improvement of symptoms in FM.
- to study parameters for exercise prescription in FM.
- To assess the association between HRV and strength improvement and HRV and clinical improvement.

### 3 – PATIENTS AND METHODS

3.1-TYPE OF STUDY: randomized, evaluator-blinded, controlled clinical trial comparing group with strengthening exercises to control group receiving treatment with stretching and flexibility exercises. Both groups will make use of cyclobenzaprine (muscle relaxant pharmacologically classified as tricyclic antidepressants) as well as simple analgesic (acetaminofen, dipyrone). No medication will be introduced.

3.2 – PATIENTS - sixty women will be enrolled from the outpatient clinic of the Rheumatology Service of University Hospital of UFES between 18 to 65 years old, classified as FM according to the ACR90 criteria (Wolfe et al., 1990), randomized and allocated in control or intervention groups. The sample size was calculated considering the comparison between the averages in the two populations with FM. For this kind of analysis we assumed that the variances will be the same and that the number of observations will be the same in both samples. We will regard as a main parameter the visual analogical scale (VAS) for pain, expected delta of improvement at least of 30%, statistical significance of 5% and power of study of 80%. We will make use of the standard-deviation by EVA for pain previously known in the Brazilian population with fibromyalgia (Valim et

al., 2003). The minimum size calculated from the above parameters was of 29 subjects for each group or a total of 58 subjects. We intend to select a greater number of subjects in case of losses.

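### The main objective is heart rate variability, but the main parameter, the sample size and the 80% power belong to pain VAS, so the main objective has no stated power

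*Protocol*

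**What the plan says.** Section 2.1 of the protocol, headed Main, has a single bullet: "To study Heart Rate Variability (HRV) in patients with FM who underwent strengthening exercise program", compared with control patients doing flexibility and stretching. Pain is not mentioned there.

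Section 2.2, headed Secondary, opens with an objective "to assess the strengthening training outcomes in the improvement of symptoms, quality of life and HRV in patients with FM", against the same control. The between-group HRV comparison is thus both main and secondary, and pain enters the objectives only through the word symptoms.

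Section 3.2 sizes the trial. It states: "The sample size was calculated considering the comparison between the averages in the two populations with FM". It continues: "We will regard as a main parameter the visual analogical scale (VAS) for pain". The expected improvement of at least 30%, the 5% significance and the 80% power follow in the same sentence. The spread is also that of pain: "We will make use of the standard-deviation by EVA for pain previously known in the Brazilian population with fibromyalgia". The result is 29 women per group, 58 in total; 60 are to be enrolled, and section 3.4 sets a minimum of 30 per group.

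Sections 3.8 and 3.8.1 describe the HRV recordings and indices. They give no HRV effect size, standard deviation or power.

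**The concern.** A trial's main objective and the variable that fixes its size normally coincide, or the plan says why they do not. Here the word main is attached to HRV in one section and to pain in another, and nothing reconciles the two.

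Two things are at stake. First, whichever of HRV and pain turns out favourably could be reported as the prespecified main result, with a sentence of the protocol to support it. Second, a null HRV result could be presented as coming from a study with 80% power, although that power was never calculated for HRV.

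A statistical analysis plan cannot settle this alone. The conflict lies between protocol sections already written, so a later plan that chose either outcome would still contradict one of them.

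**Working it through.** **1. Which outcome each statement belongs to**

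| Item | Section | Outcome |
|---|---|---|
| Main objective | 2.1 | HRV |
| Secondary objective, first bullet | 2.2 | symptoms, quality of life, HRV |
| Main parameter | 3.2 | pain VAS |
| 30% improvement, SD, 5%, 80%, 29 per group | 3.2 | pain VAS |
| HRV effect, SD or power | none | not given |

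**2. The plan's own figure**

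The pain SD and the baseline VAS are not printed, so 29 per group cannot be computed forward. It can be inverted. For two equal groups and a two-sided 5% test (an assumption, since sidedness is not stated), the normal approximation is

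d = (z₀.₉₇₅ + z₀.₈₀) × √(2/n) = (1.960 + 0.842) × √(2/29) = 0.736 SD.

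The t-test calculation gives 0.749 SD. If the 30% is a between-group difference relative to baseline, the normal-approximation figure implies SD = 0.30 × baseline / 0.736:

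| Assumed baseline VAS | Difference (points) | Implied SD (points) |
|---|---|---|
| 5 | 1.5 | 2.0 |
| 6 | 1.8 | 2.4 |
| 7 | 2.1 | 2.9 |
| 8 | 2.4 | 3.3 |

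So 29 per group is plausible for pain VAS, though it cannot be verified from the protocol. Nothing here shows it to be wrong.

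**3. What the same numbers give for HRV**

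Only standardized differences can be used. Two-sided 5%, 80% power, noncentral t:

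| Setting | Detectable difference |
|---|---|
| 30 per arm, unadjusted, no losses | 0.736, about 0.74 SD |
| 27 per arm (assumed 10% loss: 30 × 0.9), unadjusted | 0.777, about 0.78 SD |
| 30 per arm, baseline-adjusted, assumed correlation 0.5 | 0.736 × √(1 − 0.5²) = 0.637, about 0.64 SD |
| 30 per arm, baseline-adjusted, assumed correlation 0.7 | 0.736 × √(1 − 0.7²) = 0.525, about 0.53 SD |

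Power with 30 per arm, unadjusted and without losses, over assumed HRV effects:

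| Assumed effect (SD) | Power | Per arm for 80% |
|---|---|---|
| 0.3 | 21% | 176 |
| 0.4 | 33% | 100 |
| 0.5 | 48% | 64 |
| 0.6 | 63% | 45 |

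These effects are assumptions that show a range. The protocol supports none of them over the others.

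**4. If both outcomes were treated as primary**

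Two unadjusted 5% tests would carry a familywise error of 1 − 0.95² = 9.75% if independent. Splitting alpha to 2.5% each would leave about 73% power (normal approximation, 30 per arm) for the 0.736 SD effect that 29 per group implies. About 36 per group would then be needed for 80%.

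**The case against.** The best defence is that main parameter occurs only in the sample-size paragraph, between the variance assumptions and the delta, and may mean no more than the variable used for this calculation. The protocol never uses the term primary outcome, so two competing primaries is an inference. Sizing on a practical variable is legitimate, and a careful reader of section 3.2 would see that the 80% refers to pain.

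Part of this stands: the rival-primary reading is a risk that the wording creates and not something the protocol declares. But the defence still leaves the only main objective without a sample-size basis, and sizing on another outcome is acceptable only when it is declared. Section 3.2 does not say that it departs from section 2.1.

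Three stronger readings are tempting, and the protocol does not support them:

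- **That HRV is underpowered.** This needs an HRV effect and SD, and neither is given. A baseline recording is planned (section 3.8), and adjusting for it could lower the detectable difference.
- **That the many HRV indices and recordings give a large, calculable false-positive rate.** Normalised LF and HF are nearly complementary by construction, LF/HF is their ratio, and RMSSD and pNN50 both come from adjacent-interval differences. A calculation that treats them as independent would mislead. The choice of index, time point and multiplicity rule may also properly sit in an analysis plan that is not at hand.
- **That pain must become the primary outcome.** The hypothesis closing section 1 names pain and symptoms as targets and HRV as a mechanism, which is compatible with either order. The choice belongs to the authors.

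**Conclusion.** The inconsistency holds. Section 2.1 makes HRV the sole main objective, section 2.2 repeats it as secondary, and section 3.2 bases the whole sample-size argument on pain VAS. The stated 80% power does not apply to the stated main objective, and the text leaves room to present either outcome as primary.

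Its size can be given only conditionally. With 60 women the trial has 80% power for an HRV difference of about 0.74 SD. That assumes an unadjusted two-sided 5% comparison of means, 30 per arm and no losses; losses raise the figure and baseline adjustment lowers it. Whether such a difference is realistic for HRV cannot be judged from the protocol.

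**What to change.** Name one primary outcome, chosen by the authors before any outcome data are seen, and use it consistently in sections 2.1, 2.2 and 3.2. The between-group HRV comparison should appear under one heading only. The separate objective in 2.2 on the association of HRV with strength and clinical improvement is a different question and can stay.

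- **If pain VAS is primary:** restate 2.1 in terms of pain and make HRV a secondary, mechanistic outcome. The calculation in 3.2 then supports the main objective.
- **If HRV stays primary:** name one index and one time point. State in 3.2 that the 29 per group and the 80% apply to pain only. Report the HRV difference detectable with 60 women and the assumptions behind it: about 0.74 SD unadjusted with 30 per arm and no losses, about 0.78 SD with 27 per arm, and about 0.64 SD with 30 per arm and baseline adjustment at an assumed correlation of 0.5.
- **If both are to be primary:** state a multiplicity rule and recalculate the size.

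The first two routes cost wording only and leave arms and visits unchanged. The price is that the stated power becomes less favourable for HRV. The second route discloses the position but does not justify the size: if the authors want 80% power for a smaller HRV difference, the number of women would have to rise.

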### 3.3 - EXCLUSION AND INCLUSION CRITERIA:

#### 3.3.1 – Inclusion criteria:

- Classification criteria for Fibromyalgia (ACR 1990)
- Sedentary subjects (without regular physical activity in the last 3 months)
- Women between 18 to 65 years old

#### 3.3.2 – Exclusion criteria:

- Cardiovascular and/or respiratory diseases that might limit physical activity (COPD, Pulmonary Fibrosis, asthma moderate to severe, respiratory insufficiency);
- Organ dysfunction (renal, hepatic, coronary, pulmonary insufficiency);
- Arterial hypertension and diabetes mellitus;
- Uncontrolled thyroid disease;
- Autoimmune rheumatic diseases and/or non-autoimmune with symptoms that might limit the movement or physical effort;
- The use of beta blockers, calcium channel blockers and any other anti-hypertensive, anticonvulsants; non tricycles antidepressants; opioid analgesic including tramadol.
- cyclobenzaprine >10 mg/day, and amitriptyline > 25 mg/day;
- Performing or have performed exercise within the last 3 months;
- Inability to understand the questionnaires;

- Positive treadmill test for myocardial ischemia;
- Receipt of the social security benefits.

### 3.4 – STUDY PROTOCOL

The experimental group (STRE) will receive strengthening training in “Station for lifting weight exercises” (Flex Mega 8, Flex Fitness Equipment Brand) using the recommendations of the American College of Sports Medicine (ACMS, 2010), twice a week, during 45 minutes for 16 weeks. The control group (FLEX) will receive stretching and flexibility exercise training according to the protocol of prescription and previously tested and described in appendix F (Valim et al., 2003), twice a week, during 45 minutes for 16 weeks. The minimum number of patients per group will be 30. The randomization will be by arriving order of the patients at the Clinic, having 2 groups with a distribution at random one by one. There will be an examiner for the selection and unblinded randomization and another for the application of tools that will be blind. Patients will undergo clinical and cardiological evaluation with an exercise stress test (Ergometric test) request in all of them according to ACMS as one more method of evaluation for inclusion and exclusion.

The evaluation will be performed by a blind examiner, an expert physiotherapist in rheumatology and trained for the application of the tools at the beginning, after 30, 60, 90, 120 days from the treatment onset.

The measure for prescription and muscle strength gain will be by the method of maximal repetitions (Lindh et al., 1994; Tritschler, 2003; Brosseau et al., 2008; ACSM, 2010). The evaluations will take place at the beginning, 30, 60, 90, 120 days (final evaluation). Evaluations will be performed by the same blind examiner for the examined group. The training team will be formed by a physiotherapist, physical educator, and

experienced doctors at strengthening training and flexibility and stretching exercises and they must follow the following protocol.

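### Allocation has no concealment step and is run by the examiner who selects patients, so the recruiter can know or predict the next arm

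*Protocol*

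**What the plan says.** Section 3.1 labels the study a "randomized, evaluator-blinded, controlled clinical trial". The allocation rule is in section 3.4: "The randomization will be by arriving order of the patients at the Clinic, having 2 groups with a distribution at random one by one". The next sentence assigns the roles: "There will be an examiner for the selection and unblinded randomization and another for the application of tools that will be blind". One person therefore both selects patients and runs an unblinded allocation, and a second, blinded person applies the outcome tools.

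Section 3.4 then describes a clinical and cardiological evaluation with an exercise stress test, to serve "as one more method of evaluation for inclusion and exclusion". It does not say whether this comes before or after allocation.

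On numbers, section 3.2 says "sixty women will be enrolled from the outpatient clinic of the Rheumatology Service" and assumes that "the number of observations will be the same in both samples". Section 3.4 adds: "The minimum number of patients per group will be 30".

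The protocol does not describe how the sequence is generated, who holds it, how the next assignment is hidden, or at what point a woman is irrevocably enrolled.

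**The concern.** Randomization protects a comparison only if the person deciding who enters cannot tell which arm comes next. Section 3.4 puts both tasks in the same hands and provides no barrier between them.

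Many exclusions in section 3.3.2 are factual (hypertension, diabetes, listed drugs), but some need judgement: whether a cardiovascular, respiratory or rheumatic condition could restrict activity, and whether a woman can understand the questionnaires. An examiner who knows or can guess the next arm could, even unintentionally, accept, defer or decline a borderline candidate accordingly. Fitter or less painful women could then accumulate in one arm.

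Evaluator blinding acts on measurement, after the groups have formed, so it cannot undo this. Every between-arm comparison in the trial, HRV as well as pain, rests on the groups being formed by chance.

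**Working it through.** **1. What the allocation sentence allows.** Three readings fit the text.
- *Alternation by arrival.* Once the first arm is known, every later one is known.
- *A balanced random list applied in arrival order.* If the selecting examiner can see the list, the next arm is fully known. If not, it can be partly guessed from past assignments.
- *Independent randomization of each woman after irrevocable enrolment.* The next arm cannot be predicted. The protocol does not say this is done.

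**2. Do the planned numbers favour a reading?** Sixty women with at least 30 per group means exactly 30/30. Under simple randomization its probability is C(60,30)/2^60 = 0.103. The numbers therefore suggest some balancing scheme. They do not identify alternation, because a blocked random list also gives 30/30. The total may also not be fixed at 60, since section 3.2 intends to recruit above the calculated 58 to cover losses.

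**3. How guessable is each scheme?** The guesser expects the arm that is behind, or under alternation the opposite of the last one. Expected share of correct guesses over 60 patients:

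| Scheme | Correct guesses |
|---|---|
| Strict alternation | 99% (59.5/60) |
| Blocks of 2, past assignments known | 75% |
| Blocks of 4, past assignments known | 71% |
| Blocks of 6, past assignments known | 68% |
| Concealed simple randomization | 50% |

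**4. From guessing to bias.** Suppose the recruiter shifts the expected outcome of each enrolled woman by g SD in the direction that favours the guessed arm. With a share p of correct guesses, the between-arm bias is b = 2g(2p − 1). The value of g is an assumption, and no document figure supports any particular choice.
- Alternation, g = 0.05: b = 2 × 0.05 × (2 × 0.992 − 1) = 0.098 SD.
- Alternation, g = 0.1: b = 0.197 SD.
- Blocks of 4, g = 0.1: b = 2 × 0.1 × (2 × 0.708 − 1) = 0.083 SD.
- Concealed simple randomization: b = 0 for any g.

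**5. From bias to false positives.** Two-sample t-test, 30 per arm, two-sided 5%, no true effect. The noncentrality is b/√(2/30), with 58 degrees of freedom and critical value 2.002.

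| Bias b (SD) | Noncentrality | False-positive rate |
|---|---|---|
| 0 | 0 | 5.0% |
| 0.1 | 0.387 | 6.7% |
| 0.2 | 0.775 | 11.9% |
| 0.4 | 1.549 | 33.2% |
| 0.5 | 1.936 | 47.8% |

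**6. Scale.** The 29 per group in section 3.2 cannot be reproduced, because the SD is not given as a number. Worked backwards (80% power, two-sided 5%, normal approximation), it implies a standardized difference of √(2/29) × (1.960 + 0.842) = 0.736. The two-sided test is itself an assumption. A bias of 0.4 SD would be 0.4/0.736 = 54% of that difference, and a bias of 0.1 SD would be 14%.

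**The case against.** **The sentence says the distribution is at random.** This stands. A reader might infer from arrival order and one-by-one assignment that the trial uses alternation. The text does not establish that: it may mean that women are taken as they arrive and each is randomized, or that the ratio is 1:1. The document also refers to a Portuguese version, so awkward English is weak evidence of a systematic rule. Alternation is one reading, and the sentence needs to say which rule applies. The lack of concealment remains on either reading.

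**The protocol does not place allocation before the treadmill test.** This also stands. A reader might infer from the order of sentences in section 3.4 that women are excluded after their arm is known. That section is not chronological: it describes both 16-week programmes before it mentions randomization. Section 3.2 mentions classification as fibromyalgia before randomization, and section 3.6.1.4 says only that the treadmill test precedes the exercise protocol. Exclusion after allocation is not described, but it is not ruled out either.

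**The size is assumed.** Correct. The larger biases need steady steering across the trial by a recruiter who nearly always knows the next arm. Most exclusions are factual, which limits the scope. Adjusting for baseline values would remove some of the bias from steering on measured severity, though not on unmeasured factors.

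**This could sit in the statistical analysis plan.** It does not. Who allocates, by what rule and when are matters of trial conduct, and the protocol itself fixes them. Analysis cannot fully repair groups that were formed with foreknowledge.

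**Conclusion.** The concern holds in this form: the rule is ambiguous between systematic and random assignment, the selecting examiner runs it unblinded, and nothing conceals the next arm. The recruiter can know that arm fully under alternation or a visible list, and partly (about 68% to 75% of the time for block sizes 2 to 6) under an unconcealed blocked list. With some judgement in eligibility and the timing of the treadmill test unstated, selection bias can enter.

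The consequence ranges from a slight inflation (about 7% at 0.1 SD) to a severe one (about 48% at 0.5 SD) of a nominal 5% error rate. These figures assume 30 per arm, an unadjusted t-test and steering sizes chosen for illustration. They show what the design is exposed to, and they are no evidence that steering would occur. The defect should be corrected before enrolment because it bears on every between-arm comparison and is cheap to remove.

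**What to change.** Replace the allocation sentence in section 3.4 with a rule that states:
- a computer-generated 1:1 list in permuted blocks of varying size;
- the list prepared and held by an existing team member who does not select patients (section 5.0 lists a support team that could supply one), with block sizes not disclosed to the selecting examiner;
- assignments in sequentially numbered, opaque, sealed envelopes;
- each envelope opened only after clinical and treadmill eligibility and the baseline measures are complete and recorded.

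This settles which rule applies, separates selection from assignment and fixes the order of eligibility and allocation. Varying the block size matters because the exercise programmes are visible to staff, so past assignments may become known and short fixed blocks could be guessed. Some guessability at block ends remains, but far less than with a known next arm.

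Cost: protocol wording, about 60 envelopes and minor logistics. No extra patients or staff are needed, and the blocks keep the arms close to the planned equal sizes.
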